#### **Time frame**

The trial will start shortly after approval from the Danish Medicines Authority, the local Ethics Committee and the Danish Data Protection Agency. Approximately 20 patients are treated for uncomplicated appendicitis at Department of Surgery, Herlev Hospital, per month. Altogether, 14 patients are needed to complete the trial. We estimate that the inclusion of patients will take two to three months. Because of 30 days follow-up, the expected trial period is four months.

Date: 18.04.2016

[name]  
Professor, overlæge, dr.med.  
Gastroenheden - Kirurgisk Sektion D113  
Herlev Hospital  
[name]  
Tlf. [name] - Mobil: [name]  
e-mail: [contact]

Signature: [figure not shown]

[name]

## Introduction

Peritonitis is an inflammation of the peritoneum, the epithelium that lines the abdominal cavity. The inflammation can occur either locally or diffusely in the abdomen. The severity of the disease is closely related to the extent of the inflammation. A local inflammation as seen in uncomplicated appendicitis is an acute, reversible and less severe disease than diffuse peritonitis secondary to a perforation of the colon with faecal contamination throughout the abdomen. In the latter case, peritonitis can have long-term adverse consequences for the patient even with the best current treatment options.

Current practice for both local and diffuse peritonitis is surgical intervention (i.e. source control) supplemented with the systemic (intravenous) administration of antibiotics. We wish to conduct a trial to investigate a new combination and new route of administration of drugs to treat peritonitis in combination with the current standard surgical intervention. The drugs are administered intraperitoneally, i.e. locally at the site of the disease. Thereby the highest concentration of the drugs is achieved at the site of the infection: in the abdominal cavity. Therefore, we expect that the trial drugs will act more efficiently and result in fewer side effects. Further, the treatment consists of an alliance of two types of drugs. These drugs are antibiotics and a drug that improves the patients' own immune defence. This combination attacks peritonitis from more angles than the existing treatment. The antibiotics fosfomycin and metronidazole have direct antimicrobial actions. The patient's own local immune defence is strengthened by granulocyte-macrophage colony-stimulating factor (GM-CSF), which improves the function of macrophages at the site. Thereby, the bacteria can be eliminated more efficiently.

We wish to improve the treatment of patients suffering from peritonitis. This pilot trial is conducted in the healthiest group of patients suffering from local peritonitis: patients with uncomplicated appendicitis. These patients have few complications and are often ready for discharge some hours after surgery at which the appendix is removed. The intraperitoneal administration of drugs requires access to the abdominal cavity, which can only be gained by an invasive

procedure. Therefore, healthy volunteers are not suitable for this pilot trial as this kind of invasive procedure would not be justifiable.

## Background

### GM-CSF

GM-CSF is a glycoprotein cytokine, which is produced by cells of the immune system such as macrophages, monocytes and T lymphocytes, as well as by fibroblasts, endothelial cells and many types of epithelial cell. The cytokine binds to its receptor on the cell membrane and activates a signalling pathway inside the cell. Thereby, GM-CSF promotes the growth, differentiation and maturation of macrophages and neutrophil granulocytes and stimulate their activities.

Recombinant human GM-CSF has been synthesized in various host cells, such as *Escherichia coli* (*E. coli*), yeast, or mammalian cells. The following sections concern the use of the non-glycosylated recombinant human GM-CSF produced by *E. coli*: molgramostim.

Recombinant GM-CSF has been administered by different routes: subcutaneously, intravenously, and intraperitoneally. GM-CSF administered intraperitoneally improved the local immune response in patients undergoing dialysis and suffering from advanced intra-abdominal cancer. Here, an intraperitoneal sample from one patient confirmed an increase in white blood cells and neutrophil granulocytes inside the abdominal cavity. Another study also found that the numbers of macrophages, lymphocytes, and neutrophil, eosinophil and basophil granulocytes in peritoneal effluent showed a significant increase as a response to intraperitoneal administration of GM-CSF. Further, the phagocytic activity of peritoneal macrophages improved.

The subcutaneous administration route of GM-CSF has been studied in a randomised controlled trial (RCT) in patients treated for abdominal sepsis. Subcutaneously administered GM-CSF resulted in faster improvement, development of fewer infectious complications, and fewer reoperations. Further, GM-CSF was intravenously administered in an RCT in patients with severe sepsis and respiratory dysfunction admitted to the intensive care unit. GM-CSF was

associated with improved oxygenation and increased numbers of neutrophil granulocytes in the blood.

### **Fosfomycin**

Fosfomycin is an organic phosphonate antibiotic of low molecular weight and negligible protein binding, which shows a good tissue distribution. The half-life in blood of fosfomycin is approximately 2 hours. It is excreted unchanged into the urine by glomerular filtration. It enters the bacteria and inhibits the bacterial cell wall synthesis through an irreversible inhibition of the enzyme enolpyruvyl transferase. This results in a bactericidal activity on bacteria in the growth phase. Fosfomycin has a broad spectrum of activity against both Gram-positive and Gram-negative aerobic bacteria. Intravenous fosfomycin has been used for abdominal- and other severe infections and is increasingly used to treat infections with multi-drug-resistant bacteria. Its antibacterial spectrum includes *E. coli* and other *Enterobacteriaceae*, including those producing extended spectrum beta-lactamase (ESBL). Further, it shows good activity against *Staphylococcus aureus*, including methicillin-resistant *Staphylococcus aureus* (MRSA), and moderate activity against enterococci, especially *Enterococcus faecalis*, even when these are vancomycin resistant (VRE). The oral formulation, fosfomycin trometamol, is used routinely to treat uncomplicated urinary tract infections in southern Europe.

Fosfomycin has been administered intraperitoneally in patients undergoing dialysis. Both studies were pharmacological studies in patients without signs of peritonitis and suggested bidirectional exchange of fosfomycin from the blood to the abdominal cavity and vice versa. One of the studies found a better systemic absorption of intraperitoneally administered fosfomycin than penetration of intravenously administered fosfomycin into the peritoneum. This indicates that intraperitoneal administration of fosfomycin could have an advantage over intravenous administration.

### **Metronidazole**

Metronidazole is a nitroimidazole antibiotic, which has a bactericidal action on anaerobic bacteria and also kills certain protozoa, e.g. amoebae. The half-life of

metronidazole in the circulation is 6-8 hours. It is metabolised in the liver to give rise to five different metabolites, which have varying levels of antimicrobial activity that are lower than that of metronidazole. Metronidazole and its metabolites are mostly excreted into the urine. It has been estimated that less than 20% of metronidazole is bound to plasma proteins. The mechanism of action is not fully understood. However, cytotoxic intermediate metabolites interact with bacterial DNA and result in destabilisation.

Because of its anaerobic coverage, it plays a prominent role in both the prophylaxis and treatment of intra-abdominal infections. Metronidazole is usually administered intravenously, orally or rectally. However, vaginal and topical routes of administration routes also exist.

Metronidazole has been given intra-abdominally. One study examined 500 mg metronidazole and 500 mg cephadrine installed in the peritoneal cavity and wound in 46 patients undergoing laparotomy where faecal or purulent peritonitis or faecal contamination of the wound was present. The antimicrobial agents were left for 1½ hours before they were drained through draining tubes. Another study applied 500 mg or 1 g metronidazole to the abdominal cavity, which was removed through drains after 2 hours, in 182 patients with faecal or purulent peritonitis or faecal soiling of the abdominal cavity. These patients also received intravenous administration of antimicrobial agents. Finally, a study, which divided a total of 100 patients with complicated appendicitis into intervention and control groups, administered both intravenous antimicrobial agents and a local installation of 500 mg of metronidazole and 1 g of cephazolin in the peritoneal cavity and wound layers in the intervention group. The control group only received the intravenously administered antimicrobial agents and had more early complications than the intervention group. None of the abovementioned studies made pharmacokinetic investigations.

### **The combination of the drugs**

The combination of GM-CSF, fosfomycin, and metronidazole has to our knowledge not been given before. However, fosfomycin and metronidazole has previously been co-administered intravenously to patients undergoing

abdominal surgery. Both for elective and emergency surgery the combination was effective. It was more effective than control treatment with metronidazole and gentamicin in a study of emergency surgery. Therefore, we expect the combination of these antibiotics intraperitoneally to be a reasonable alternative treatment to the current combination of intravenously administered beta-lactam antibiotics and metronidazole. A previous RCT treated abdominal sepsis with antimicrobial agents intravenously together with subcutaneously administered GM-CSF. These patients improved faster, developed less infectious complications, and needed fewer reoperations. Therefore, we expect the stimulation of the patients' local immune defence by GM-CSF to have an additive or synergic effect with respect to antimicrobial therapy alone.

### **The dosages of the drugs**

We have chosen doses of 50 µg of GM-CSF (molgramostim) 4 g of fosfomycin, and 1 g of metronidazole. The chosen doses are based on doses from previous studies and clinical practice.

Intraperitoneal doses of GM-CSF of 68 µg/day were administered in patients undergoing peritoneal dialysis and intraperitoneal doses of 1, 2, 4, or 8 µg/kg/day were administered to patients with advanced intraperitoneal malignancy. Pharmacokinetic studies have administered escalating intravenous doses of GM-CSF of 1, 2, 4, or 8 µg/kg/day to patients with advanced intraperitoneal malignancy, 0.3, 1, 3, 10, 15, and 20 µg/kg/day to patients with advanced malignancy and/or neutropenia, and 3 µg/kg or 5.5 µg/kg to patients with malignant lymphomas. An RCT administered an intravenous dose of 3 µg/kg/day to patients requiring admission to the intensive care unit. Pharmacokinetic studies administered subcutaneous doses of GM-CSF of 5.5 µg/kg to patients with malignant lymphomas, and 0.3, 1, 3, 10, 15, 20, and 30 µg/kg/day to patients with advanced malignancy. In an RCT patients with abdominal sepsis received subcutaneous doses of 3 µg/kg/day.

Our chosen dose of 50 µg of GM-CSF is low compared to these studies. This conservative dosing regimen decreases the risk of adverse effects but is expected to be high enough to have a local intra-abdominal effect.

The two previous pharmacokinetic studies on fosfomycin administered intraperitoneally used doses of 1 g and 4 g. The previous studies where intravenous fosfomycin was administered during emergency abdominal surgeries used a dose of 4 g. For the treatment of severe infections the recommended intravenous dosage is 12-24 g daily divided into 3-4 doses. Our chosen dose of 4 g is at the same level as previous studies and current clinical practice.

It is clinical practice to give a systemic, intravenous infusion of metronidazole in combination with other antimicrobial agents during emergency surgical procedures or when contamination of the abdominal cavity is expected. The standard hospital guideline for a single dose is 1 g of metronidazole, whereas continuous treatment consists of 1-1.5 g of metronidazole daily divided into 2-3 doses. The previous studies with intra-abdominal administration used 500 mg to 1 g. We have chosen a dose of 1 g of metronidazole, which is within the range of the above-mentioned doses.

The combined dosages will only be administered once – during surgery – which is similar to the current clinical practice for the intravenous administration of antibiotics during surgery for uncomplicated appendicitis.

### **The formulation of the drugs**

The formulation of fosfomycin Fomicyt/Infectofos manufactured by Infectopharm is used in this trial and approved for clinical use in Germany. The 4 g of fosfomycin will be diluted in 300 ml of sterile water.

Metronidazole is available in our department as 100 ml *Metronidazol "B. Braun"*, which has a concentration of 5 mg/ml. We will use 200 ml of metronidazole.

The GM-CSF used will be Repomol (molgramostim) from Reponex Pharmaceuticals A/S, which consists of recombinant human GM-CSF expressed in *E. coli* bacteria. We will use a dose of 50 µg in 0.2 ml of solution (water for injections).

The total volume administered intraperitoneally will be 500 ml.

## **Intraperitoneal administration of the drugs**

Intraperitoneal administration of antimicrobial agents has been recommended in the treatment of peritonitis associated with peritoneal dialysis and is accepted clinical practice at our hospital.

The drugs will be administered through an already established access to the abdominal cavity. During a laparoscopic appendectomy, three small accesses are made. These are used for a camera and instruments. One of these instruments includes a suction tube used both for suction of excess fluid and irrigation with saline. When the removal of the appendix is completed and haemostasis is secured, the abdominal cavity will be irrigated with a minimum of 500 ml of saline. Hereafter, the drugs will be administered into the intraperitoneal space through the suction tube.

## **Trial**

The trial will consist of a main trial of safety and a sub-trial on pharmacokinetics. These involve and will be recruited from the same trial population of patients. The main trial on safety and the sub-trial on pharmacokinetics will be described independently in the following sections.

## **Main trial: Safety**

### **Aim**

We wish to evaluate the safety of the intraperitoneal administration of the combination of fosfomycin, metronidazole, and GM-CSF.

### **Primary outcome**

The safety of intraperitoneal administration is evaluated through the white blood cell counts 4 hours postoperatively. A toxic effect is defined by a drop below the lower reference range.

### **Secondary outcomes**

Repeated biochemical markers (including a white blood cell differential count, inflammation marker C-reactive protein (CRP), kidney function tests, liver

function tests, and electrolytes), vital signs (blood pressure, pulse, frequency of respiration, peripheral saturation (SAT), and temperature,), length of stay, side effects, and adverse events until 30 days after surgery.

## **Design**

An open-label, phase II, pilot study of 14 participants.

## **Trial participants**

Inclusion criteria:

- Men  $\geq 18$  years old
- Suspicion of acute appendicitis and planned for diagnostic laparoscopy and eventual appendectomy
- Written informed consent after written and verbal information

Exclusion criteria:

- Cannot understand, read or speak Danish
- Previous allergic reaction to fosfomycin, metronidazole, or GM-CSF
- Perforated appendicitis (diagnosed either during surgery or at a preoperative computer tomography (CT) scan)
- Diagnostic laparoscopy revealing normal appendix not requiring an appendectomy
- Other intra-abdominal pathology requiring surgical intervention (diagnosed either during surgery or at a preoperative CT-scan)
- Known renal or hepatic disease or biochemical evidence at the time of admission
- Known autoimmune disease or other chronic inflammation
- Known hematologic disease or cancer
- Previous abdominal surgery (either laparoscopic or open surgery)
- Daily use or use of medication one week prior to or during the trial period apart from painkillers such as paracetamol, ibuprofen, tramadol, and morphine as well as drugs needed for anaesthesia, thrombosis prophylaxis, and nausea. Limitations for antibiotics are defined below

- Use of other antimicrobial agents than the trial treatment one month before until 24 hours after the trial treatment
- Participant in another drug trial one month prior to the date of the surgery
- Body mass index  $\geq 35$  kg/m^2
- Weekly intake of alcohol >14 units, where one unit corresponds to 12 g alcohol

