### **Trial course**

The trial course is outlined in Figure 1. Patients are admitted to the Department of Surgery, Herlev Hospital, with suspected acute appendicitis and a general panel of blood samples are collected. A surgeon from the department will either plan for an acute surgery or keep patients for further observation. The primary investigator of the trial approaches these otherwise healthy patients to give information about the trial. Thereby we ensure the patient has plenty of time for consideration in this setting where an acute disease is involved. Patients, who fulfil the inclusion criteria and present none of the exclusion criteria, apart from those criteria that can only be clarified at surgery, are enrolled in the trial after informed consent. Baseline characteristics of the enrolled patients will be noted in the case report form (CRF). A note of the patient's enrolment in the trial will be added to the patient's medical record, so the standard intravenous antibiotics are not administered. The patients are included in the trial during the surgery when the operating surgeon or a supervisor visually confirms the diagnosis of uncomplicated appendicitis. Patients that fulfil any exclusion criteria are excluded from the trial and will receive treatment and antibiotics according to standard clinical practice. Included patients will have their appendixes removed laparoscopically according to standard clinical practice. When the appendix has been removed from the abdominal cavity through an Endobag and haemostasis has been secured, a minimum of 500 ml of saline will be used for irrigation of the abdominal cavity. Hereafter the trial treatment will be instilled into the abdominal cavity under the supervision of the trial investigator to ensure full compliance. The patients will have vital signs measured at baseline, 5 minutes, 10 minutes, 15 minutes, 4 hours and 12 hours after the trial treatment during

their hospital admission. These values will be noted in the CRF. Participants will be peri- and postoperatively monitored according to standard practice.

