Postoperatively, the general panel of blood samples will be repeated 4 hours after the trial treatment, which differs from standard clinical practice. Side effects are evaluated through the following procedures. The primary investigator will perform an objective examination of the participant and ask if any changes have risen 12 hours after the trial treatment has been administered. This will be noted in the CRF. When the patient has a “Postanesthetic Recovery Score for Patients Having Anesthesia on Ambulatory Basis” (PARSAP)  $\geq 18$  and is informed about the procedure the patient will be discharged according to clinical practice. PARSAP is found in Supplements, Table 2.

Ten days after the trial treatment has been administered side effects will be evaluated again. The primary investigator will meet with the participant to perform an objective examination and ask if any changes have risen since the surgery. This will be noted in the CRF.

A follow-up of the participants will be performed 30 days after the surgery through medical records and contact to the participant by telephone, which will be noted in the CRF.

[figure not shown]

*Figure 1. The trial course for participants in the main trial: Safety. An outline (black text) of the normal course of admission for appendicitis is seen at the bottom. The timespan for enrolment and inclusion are marked in grey boxes. All investigations related to the trial are shown in blue text and in the blue boxes. These include blood samples, vital signs (pulse, blood pressure, temperature, frequency of respiration, and SAT), and objective examinations combined with questions about any changes to evaluate side effects. Finally, a follow-up will be conducted 30 days after the surgery. The measurement of vital signs during the surgery will be performed at baseline, 5, 10 and 15 minutes after the trial treatment has been administered.*

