### Withdrawal and dropout criteria

The participants can withdraw their consent at any point during the trial. If the participant becomes unstable during the surgery, the primary investigator can exclude the participant from the trial for the safety of the participant. This will be effectuated in case of:

- Severe intra-abdominal bleeding
- Allergic reaction to general anaesthesia
- Other severe complications during surgery

A participant has concluded the trial when the 30-day postoperative follow-up has been conducted.

The trial will be stopped if severe adverse effects or severe complications, which are not expected, arise from the trial treatment. This will be decided by the sponsor.

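### Exclusion and intraoperative withdrawal rules are not confined to the time before dosing, so a treated participant can leave the safety trial because of a possible harm, and follow-up after that is not secured

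*Protocol*

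**What the plan says.** All references are to the protocol.

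- **Trial participants (exclusion criteria).** One criterion is "Use of other antimicrobial agents than the trial treatment one month before until 24 hours after the trial treatment". Another is "Daily use or use of medication one week prior to or during the trial period apart from painkillers such as paracetamol, ibuprofen, tramadol, and morphine", with further exemptions for drugs used for anaesthesia, thrombosis prophylaxis and nausea.
- **Trial course.** The consequence of meeting a criterion is: "Patients that fulfil any exclusion criteria are excluded from the trial and will receive treatment and antibiotics according to standard clinical practice". No time limit is attached.
- **Withdrawal and dropout criteria.** "If the participant becomes unstable during the surgery, the primary investigator can exclude the participant from the trial for the safety of the participant". The grounds are severe bleeding, allergy to the anaesthetic, and "Other severe complications during surgery". The pharmacokinetic sub-trial repeats the rule. A participant finishes the main trial at the 30-day follow-up.
- **Figure 1 caption.** "The measurement of vital signs during the surgery will be performed at baseline, 5, 10 and 15 minutes after the trial treatment has been administered". The single dose is itself given during the operation (The dosages of the drugs).
- **Time frame.** "Altogether, 14 patients are needed to complete the trial". The Design section describes a study of 14 participants.
- **Measurements.** Adverse events are registered from surgery to day 30. Nothing is said about whether this continues for someone excluded after dosing.

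**The concern.** An exclusion criterion normally decides who enters. Here the later part of two criteria can be met only once the drug has been given, and the withdrawal rule covers a stretch of surgery that includes the first minutes after instillation. The events that would trigger removal overlap with what a safety trial is looking for:

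- Early rescue antibiotics may signal that the trial regimen has failed, a possibility that the Pros and cons section accepts.
- Rash is among the common GM-CSF effects in Table 1, and skin reactions are reported with the antibiotic pair. A drug given for them is not on the exempt list.
- Vital signs are a secondary safety outcome, and instability is a ground for exclusion. In an open-label trial, whether an event is a surgical complication or a drug effect is the investigator's judgement.

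If participants removed in this way are not followed or not counted, the event leaves the numerator and the person leaves the denominator, which favours a conclusion of safety. With 14 participants and no control group, one lost event can change the summary.

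**Working it through.** **Step 1: can the rules act after dosing?**

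| Rule | Window | Relation to dosing |
|---|---|---|
| Other antimicrobials | one month before to 24 h after treatment | last 24 h are post-dose, and run past the 4 h primary measurement |
| Non-exempt medication | one week before, and during the trial period | a participant's trial ends at day 30, so mostly post-dose |
| Severe complications in surgery | whole operation | includes the 5, 10 and 15 minute post-dose readings |

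Drug use in the 24 h after treatment cannot be assessed before treatment. If exclusion is pre-dose only, those clauses have no function. If they have a function, they remove treated participants. The text needs correcting on either reading.

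**Step 2: is there a figure in the plan to reproduce?** No. The Statistics section says that 14 does not come from a power calculation, and it gives no event rate or dropout rate. What follows is illustration.

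**Step 3: one reactor dropped (exact Clopper-Pearson 95% limits).**

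- Dropped and replaced: 0/14 = 0%, upper limit 1 − 0.025^(1/14) = 0.232, so 0 to 23.2%.
- Same participants, all kept: 1/15 = 6.7%, 0.2 to 31.9%.
- Dropped and not replaced: 0/13 = 0%, upper limit 1 − 0.025^(1/13) = 0.247. All kept: 1/14 = 7.1%, 0.2 to 33.9%.
- Two dropped and replaced: again 0/14. All kept: 2/16 = 12.5%, 1.6 to 38.3%.

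The distortion therefore does not depend on replacement. It depends on whether the dropped participant is still counted.

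**Step 4: expected effect.** Let p be the true event rate and q the share of events that lead to removal with the data dropped. Both are assumptions. The rate among those retained is p(1 − q)/(1 − pq). With replacement up to 14, the expected number treated is 14/(1 − pq).

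Example, p = 10% and q = 50%: 0.10 × 0.50/(1 − 0.05) = 0.05/0.95 = 5.3%. The chance of at least one event among 14 retained is 1 − (1 − 0.0526)^14 = 53.1%, against 1 − 0.9^14 = 77.1% if everyone is kept. Expected number treated: 14/0.95 = 14.7.

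Chance of seeing at least one event in 14:

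| p | all kept | q = 25% | q = 50% | q = 100% |
|---|---|---|---|---|
| 5% | 51.2% | 41.8% | 30.5% | 0% |
| 10% | 77.1% | 67.4% | 53.1% | 0% |
| 20% | 95.6% | 91.0% | 80.8% | 0% |

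In this model the direction is always downwards. The size is set by p and q, which the protocol does not give.

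**The case against.** The case on the other side is substantial.

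- **Order of events.** In the Trial course section, the exclusion sentence follows visual confirmation of the diagnosis and precedes removal of the appendix and instillation. Excluded patients get standard antibiotics, and the Pros and cons section says the same of those excluded during surgery. This stands as evidence of intent, but it does not explain clauses that can operate only after dosing.
- **Replacement.** A reader might infer that enrolment continues until 14 participants have completed. The protocol never says so. The Time frame wording can mean only that 14 are needed for the trial to be finished, and Design speaks of 14 participants. This stands.
- **Discarded data.** A reader might also infer that events vanish. No section says so. Adverse events are registered to day 30, serious ones go to the sponsor at once, and unexpected severe effects of the treatment can stop the trial. Analysis sets may be defined in an analysis plan that is not shown. This stands as to analysis. It does not settle conduct: an analysis plan cannot recover visits that were never made.
- **Narrow triggers.** Bleeding is mainly a pre-dose ground, because haemostasis is secured before instillation, and the anaesthetic-allergy ground names a different cause. Painkillers and anti-nausea drugs are exempt. The GM-CSF first-dose reaction is described at 60 ± 40 minutes after intravenous dosing, and was not seen after intraperitoneal dosing. This stands: the routes left are the open-ended complications ground and the two medication criteria.
- **Primary outcome.** It would be too strong to say that the trial selects on its primary outcome. That outcome is a low white cell count at 4 h. Neither medication criterion refers to it, and someone given antibiotics after 4 h may already have the count.

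**Conclusion.** The concern holds in limited form. The protocol contains exclusion clauses that can be met only after dosing, attaches removal from the trial to them without a time limit, and has an intraoperative ground for exclusion that does not stop at instillation. It nowhere secures follow-up or counting of a participant removed after treatment. That is a defect in a stated rule, not merely detail left to an analysis plan.

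The documents do not support the firmer statement that reactors will be replaced and toxicity will be understated. Understatement follows only if removed participants are not followed or not counted, and the protocol is silent on both. The contrast between 0/14 (0 to 23.2%) and 1/15 (0.2 to 31.9%) shows what one such loss would do. The intervals overlap widely, and the figures further assume replacement. The probabilities for p and q rest wholly on assumed values. This should be fixed, but it does not show the design to be unsound.

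**What to change.** 1. State that exclusion from the trial population applies only to criteria met before instillation.
2. Reword the post-dose parts of the two medication criteria as concomitant-medication restrictions. A breach is recorded as a protocol deviation. In the pharmacokinetic sub-trial, affected participants are flagged or examined in a sensitivity analysis.
3. State that everyone who receives any trial drug stays in the safety analysis and, consent permitting, has all assessments to day 30, whatever drug use or intraoperative event follows.
4. State whether 14 means participants dosed or participants who complete follow-up. If extra participants may be recruited, say that those already dosed are still counted.

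These changes concern counting and follow-up only. They leave the investigator's clinical management of an unstable patient as it is.

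The cost is protocol wording. The reported toxicity rate may be slightly less favourable, and concomitant drugs may add some noise to the laboratory values.
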